### Randomization

Randomization is conducted using a selection and documentation procedure that ensures balanced enrollment over time, blinds the TTS to the assignment, and prevents postrandomization assignment changes. Each site randomly assigns 450 patients on a 2:1 ratio (300 AR + IVR: 150 UC) using secure, preprinted, sequentially numbered randomization envelopes. The study statistician developed a randomization algorithm using a predetermined randomization sequence with permuted blocks of randomly varying size. The block size is masked from all except the data coordinating center (DCC) statistician and programmer. This strategy ensures balanced enrollment over time and eliminates the ability of the TTS to guess assignment prior to randomization.

The randomization algorithm matches group assignment to a four-digit randomization number, where the first digit is the site ID (KP = 1; OHSU = 2) and the last three digits are the randomization sequence number. The randomization number is printed on a label and affixed to the outside of each randomization envelope. Inside each envelope are two identical self-adhesive labels printed with the randomization number and treatment arm assignment. The labels are used to confirm and track randomization. The envelopes are placed in a box in ascending order. The treatment arm assignment is not discernable from the outside of the sealed envelope.

Once a patient is prescreened eligible, the TTS selects the next randomization envelope in sequence, along with other patient enrollment forms, and proceeds to the patient’s room. After the eligible patient provides informed consent and completes baseline assessment, the TTS opens the randomization envelope and records the participant’s assignment. At the KP site, the TTS affixes one of the randomization labels to the site’s randomization log, and then records the date and time of randomization, the participant ID number, and the TTS’ initials on the log. A second label is affixed to the enrollment checklist form before transmission to data entry staff. At the OHSU site, the TTS opens the randomization envelope, places one of the randomization labels in the patient’s research chart, records the date and time of randomization, participant ID number, and the TTS’ initials. A second label is affixed to the enrollment checklist before transmission to KP data entry staff.

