#### *Power*

A 2:1 ratio of AR + IVR to UC for 900 randomized participants will provide adequate power to detect an eight percentage point difference in thirty-day point prevalence abstinence at six months (our primary outcome), assuming an unbiased method of assigning an outcome to nonrespondents. The unbalanced design requires 864 participants to achieve 80% power, with two-tailed α set at .05, to detect a difference in thirty-day abstinence of eight percentage points between treatment groups. We expect the UC group will achieve a 15% abstinence rate, based on analyses of EMR data (unpublished) for similar populations at each site. An odds ratio of 1.65 for patients with >30 days of follow-up [3] results in a 23% expected abstinence rate for the AR + IVR group. The power calculations were conservative [25-28] and no continuity correction was applied. Rounding up to 900 total participants added an additional measure of conservatism.

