Model 1 specifies only one source of systematic variation among the trial conditions, C_k_. Any factor other than the intervention that favors one condition over the other serves to bias the estimate of the intervention effect. Since this is a randomized trial, there are no differences expected between treatment and control arms in the distribution of covariates. However, there might be unmeasured factors at the various sites that might result in varying effect sizes between the two arms. These factors are potentially confounded with site. In the adjusted analysis, site, interaction between site and treatment, and measured covariates are added to the analysis to reduce confounding and to improve the precision of the estimate of the intervention effect. Covariates can be measured at the site or patient level. Covariates measured at the group (site) level and patient level are distinguished as **G** and **M**. With covariates at two levels and patients nested within sites, we shift to a two-level generalized linear model with logit link. Level 1 involves patient-level variables: $\text{logit}\;\left[Y_{\text{ick}}\right]=\beta_{0c}+\beta_{1c}X_{k}+\beta_{2c}M_{i}+e_{\text{ick}}$, where **M**_i_ is a vector of patient-level covariates (bold indicates a vector throughout this section), *β*_0c,_*β*_1c_, and ***β***_2c_ are patient-level parameters that are allowed to vary over sites, and c = 1, . . ., C clinical sites, and e_ick_ is the residual.

The level-1 model implies three level-2 equations to model variation between sites in patient-level parameters and adds the effect of site-level covariates:

where γ_0._, γ_1_., γ_2_ are parameters to be estimated, Sc is the vector of c-1 site indicators, Gc is the vector of site-level covariates, and u are residual terms. The resulting combined two-level model is of the form:

(1)$$\text{logit}\;\left[Y_{\text{ick}}\right]={ϒ}_{00}+{ϒ}_{01}Sc+{ϒ}_{02}Gc+u_{0c}+\left[{ϒ}_{10},+,{ϒ}_{11},S,c,+,{ϒ}_{12},G,c,+,u_{1c}\right]X_{k}+\left[{ϒ}_{20},+,{ϒ}_{21},S,c,+,{ϒ}_{22},G,c,+,u_{2c}\right]M_{i}+e_{\text{ick}},$$

that simplifies to (Model 2):

(2)$$\text{logit}\left[Y_{\text{ick}}\right]={ϒ}_{00}+{ϒ}_{01}Sc+{ϒ}_{02}Gc+\left[{ϒ}_{10}+u_{1c}\right]X_{k}+{ϒ}_{11}S{\text{cX}}_{k}+{ϒ}_{12}G{\text{cX}}_{k}+\left[{ϒ}_{20}+u_{2c}\right]M_{i}+{ϒ}_{21}ScM_{i}+{ϒ}_{22}GcM_{i}+u_{0c}+e_{\text{ick}},$$

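### The adjusted model always carries a site-by-treatment term but names no trial-wide adjusted effect; under 0/1 site coding its treatment coefficient would be one hospital's effect, less precisely estimated

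*Protocol article*

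**What the plan says.** The primary test for Specific Aim 1 is Model 1, a logistic regression on treatment alone with a score test. The adjusted analysis (Model 2) then extends it: "In the adjusted analysis, site, interaction between site and treatment, and measured covariates are added to the analysis to reduce confounding". The same sentence adds a second purpose: "to improve the precision of the estimate of the intervention effect". No condition is attached to the interaction.

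The site term Sc is defined as a vector with one fewer indicator than there are sites, so two hospitals give one column. In Model 2 it appears alone and multiplied by treatment. The treatment part is therefore γ10 plus a random term, plus γ11 times site, plus γ12 times the group-level covariates G. The paragraph after Model 2 gives γ11 = 0 as the test of homogeneity. It does not say that the term is dropped if the test is not significant, and it names no average over hospitals as the adjusted intervention effect.

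Under Randomization: "Each site randomly assigns 450 patients on a 2:1 ratio (300 AR + IVR: 150 UC)".

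**The concern.** With one 0/1 site indicator S and its product with treatment, γ10 is the treatment log odds ratio where S = 0 (the reference hospital), and γ10 + γ11 is the one where S = 1. Neither is the effect for the trial. With the G-by-treatment terms also present, γ10 narrows to the reference level of G. Under Covariates and effect modifiers, G includes insurance type and inpatient care unit.

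The adjusted estimate will normally be read beside the primary one. If it is taken from the treatment line of the Model 2 output, the two estimates answer different questions. The adjusted one could lose significance or change size because of the coding alone. This matters more here because the article itself expects the hospitals to differ: the Discussion foresees easier integration of inpatient and outpatient care at KPNW than at OHSU. If the odds ratios were, say, 1.3 and 2.2 (assumed), the coefficient would be log 1.3 or log 2.2 according to which hospital is the reference.

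**Working it through.** **Inputs.** From Power: "We expect the UC group will achieve a 15% abstinence rate"; the odds ratio taken from the literature "results in a 23% expected abstinence rate for the AR + IVR group"; the test is "with two-tailed α set at .05"; "no continuity correction was applied". From Randomization: 300 AR + IVR and 150 UC per hospital, two hospitals.

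**The plan's own figure.** "The unbalanced design requires 864 participants to achieve 80% power". With 2:1 allocation the pooled proportion is (0.15 + 2 × 0.23)/3 = 0.2033. The UC group size is

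n = [1.960 × √(1.5 × 0.2033 × 0.7967) + 0.842 × √(0.15 × 0.85 + 0.23 × 0.77/2)]² / 0.08² = (0.966 + 0.391)²/0.0064 ≈ 287.9, so 288.

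The total is 288 + 576 = 864, as stated. Power at 900 is 81.7%. The inputs are therefore read as the plan intends.

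**Treatment effect on the log odds scale.** Odds are 0.23/0.77 = 0.2987 and 0.15/0.85 = 0.1765. The ratio is 1.69 and its log is 0.526.

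**Treatment coefficient without the interaction** (treatment and site, equal rates at both hospitals, all 900 patients):

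SE = √[1/(600 × 0.23 × 0.77) + 1/(300 × 0.15 × 0.85)] = √(0.00941 + 0.02614) = 0.189.

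**Bare treatment coefficient with 0/1 site and the interaction** (only the 450 patients of the reference hospital inform it):

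SE = √[1/(300 × 0.23 × 0.77) + 1/(150 × 0.15 × 0.85)] = √(0.01882 + 0.05229) = 0.267.

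The ratio is √2 = 1.41.

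**Wald power for that coefficient, two-sided 0.05.** Without the interaction: 0.526/0.189 = 2.79, and Φ(2.79 − 1.96) ≈ 0.80. With it: 0.526/0.267 = 1.97, and Φ(1.97 − 1.96) ≈ 0.51.

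**Same fit, averaged over hospitals.** The contrast γ10 + ½γ11 is the mean of two independent hospital estimates. Its SE is √(0.267² + 0.267²)/2 = 0.189, so nothing is lost against the model without the interaction.

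**Unequal baseline rates** (UC rates by hospital are assumed; the odds ratio stays at 1.69 at both). The range in the third column depends on which hospital is the reference.

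| UC rates | SE, no interaction | SE of bare coefficient, 0/1 coding | Increase | SE ratio, centred coding |
|---|---|---|---|---|
| 15% / 15% | 0.189 | 0.267 | 41% | 1.00 |
| 12% / 18% | 0.189 | 0.249 or 0.292 | 32% or 54% | 1.01 |
| 10% / 20% | 0.191 | 0.240 or 0.315 | 26% or 65% | 1.04 |

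In none of these cases does the interaction make the intervention effect more precise.

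**The case against.** The strongest reply has four parts.

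- **Coding.** The article speaks of indicators but fixes neither a reference hospital nor a parameterisation. With centred coding the loss is nil or slight. This stands: the one-hospital reading and the 41% are conditional on 0/1 coding. That is, however, the ordinary meaning of an indicator, and the article offers no other.
- **Which estimate is reported.** A reader might infer that γ10 will be published as the adjusted result, and so that the adjusted analysis has half the information. The article does not say so. The fitted model holds the full information, since the average over hospitals has SE 0.189; only the single coefficient is weaker. The choice of contrast could also sit in an analysis plan that is not shown. What remains is more than an omission: the printed model and the purpose given for it do not fit together.
- **Simplification.** The figures come from a model with treatment, site and their interaction only. Model 2 also has G-by-treatment terms, patient covariates with their interactions, and random site terms, so 41% is not the exact figure for Model 2. This stands too. The additional treatment interactions make γ10 harder, not easier, to read as a trial effect.
- **Purpose.** The precision rationale is given for site, interaction and covariates jointly, and looking for different effects at the two hospitals is a legitimate aim of this trial. Both are true. The aim is met equally well by a separate heterogeneity analysis.

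A reader might also infer that the trial's main conclusion or its power is at risk. It is not: the primary analysis is Model 1 without site terms, and 864 and 900 refer to that comparison.

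**Conclusion.** The point holds for the secondary adjusted analysis only. As printed, Model 2 includes the site-by-treatment term unconditionally, identifies no trial-wide adjusted effect, and is said to sharpen an estimate that the interaction cannot sharpen in any of the cases checked.

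The SE increase of about 41% and the fall in Wald power from about 80% to about 51% rest on 0/1 site coding, the simplified model, equal hospital sizes and 15% v 23% at both hospitals. The range of 26% to 65% rests on assumed differences in baseline rates. Under centred coding, or for an average of the two hospital effects, the SE is about 0.189 with equal rates and at most 4% above the no-interaction value in the unequal cases. The matter should be settled before analysis, because the result would otherwise depend on an arbitrary choice of reference hospital.

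**What to change.** State in the analysis section or the analysis plan that the adjusted overall effect is the treatment coefficient from a model with treatment, site and baseline covariates, without site-by-treatment or other treatment interactions. If a single model is preferred, code site as ±½ and name the resulting equally weighted average over the two hospitals as the adjusted effect; G-by-treatment terms would then have to be left out or centred as well.

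Keep the site-by-treatment term in a separate heterogeneity analysis that reports the two hospital-specific odds ratios and their ratio with a 95% confidence interval. Reword the precision rationale so that it refers to site and baseline covariates, not to the interaction.

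The cost is a sentence or two of text and one extra model fit. Data collection, sample size and the primary test do not change.

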#### *Specific Aim 1: estimate self-reported thirty-day abstinence at six and twelve months for patients assigned to receive inpatient AR + IVR compared to usual care*

Based on KPNW and OHSU member data and meta-analyses of effectiveness of hospital cessation programs with ≥1 month postdischarge follow-up, we expect about 15% of usual care patients and 23% of AR + IVR participants will be abstinent six months following discharge. The primary analysis assumes that nonrespondents are smokers.

The treatment effect on the primary outcome (and other binary outcomes) will be evaluated using logistic regression, logit[Y_ik_] = β_0_ + β_1_X_k_ + e _ik_ (Model 1), where Y_ik_ is the binary indicator of the observed binary smoking status for the i^th^ patient (i = 1,. . .,n_k_) within the k^th^ treatment condition (k = 1,2), X_k_ is the fixed effect of the k^th^ condition, that is, intervention or control, and β_0_, β_1_ are parameters to be estimated. Any difference between the predicted and observed values is left to the residual error (e _ik_) in this model. Multiple regression methods available in SAS PROC Logistic [33] will be used to estimate the parameters of this generalized linear model. The intervention fixed effect will be tested using the score *χ*^2^ test.

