Abstinence and cost data are used to calculate the incremental net cost per additional quit for AR + IVR participants compared to UC participants. Incremental total costs and cost per participant, by payment source are reported. Incremental cost-effectiveness ratios (ICERs) are measured as: a) incremental intervention costs per incremental quit from health plan/insurer and patient perspectives; b) incremental total costs (intervention plus health care expenditures during follow-up) per incremental quit from health system/insurer and patient perspectives; c) incremental intervention costs per incremental quality-adjusted life-year (QALY) saved from a societal perspective; and d) incremental total costs (intervention plus health-care expenditures during follow-up) per incremental QALY saved from a societal perspective. QALYs for each intervention arm are estimated using life expectancy data and responses from interviewer-administered EQ5D-5L.

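### The adjusted logistic model is justified by less confounding and better precision, which its log odds ratio will not show; report a standardized risk difference from baseline covariates instead

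*Protocol article*

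**What the plan says.** Specific Aim 1 of the protocol article sets out two logistic models. Model 1 contains treatment only and carries the main test: "The intervention fixed effect will be tested using the score" chi-square statistic. Model 2 is the adjusted one: "In the adjusted analysis, site, interaction between site and treatment, and measured covariates are added to the analysis", and the stated purpose is "to reduce confounding and to improve the precision of the estimate of the intervention effect". Shortly before, the same section says: "Since this is a randomized trial, there are no differences expected between treatment and control arms in the distribution of covariates". It then raises unmeasured site factors that might make the effect differ in size between sites.

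The section on covariates and effect modifiers lists the candidates for adjustment. Most are baseline characteristics. Two are not: the cessation program and the medications that the patient used.

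Two other sections work on the scale of proportions. The Power section sizes the trial "to detect a difference in thirty-day abstinence of eight percentage points between treatment groups". Specific Aim 3 says: "Abstinence and cost data are used to calculate the incremental net cost per additional quit".

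**The concern.** Model 2 has a logit link, so its treatment estimate is a log odds ratio. Both halves of the rationale are doubtful for that quantity.

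- **Confounding.** Randomization removes systematic confounding, as the section itself says. Site cannot be a systematic confounder either, because the Randomization section fixes 300:150 within each site. An effect that varies between sites is effect modification. What adjustment can correct is chance imbalance, which the text does not mention.
- **Precision.** Adjusting a linear model for prognostic covariates shrinks the standard error of the treatment effect. In a logistic model it does not. The conditional odds ratio is a different quantity from the marginal one, and its log has a larger standard error.

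A reader who has been told that Model 2 reduces confounding may see a larger adjusted odds ratio and conclude that the crude result was biased towards no effect. The real benefit of adjustment does not show in the reported standard error, and the article describes no covariate-adjusted estimate on the risk-difference scale that the power statement and the cost per quit use.

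**Working it through.** **Inputs from the article.** Six-month abstinence: "we expect about 15% of usual care patients and 23% of AR + IVR participants will be abstinent six months following discharge". Allocation is 2:1 with 900 patients, so 300 UC and 600 AR + IVR. Two-sided alpha is 0.05, power 80%, no continuity correction, required total 864.

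**Assumed.** The article gives no prognostic strength for the covariates. I take a normally distributed covariate score with SD s = 0.5 to 1.0 on the logit scale (c-statistic about 0.63 to 0.75). All 900 patients are taken as analyzed; deaths, which the article excludes from the primary analysis, would lower this a little.

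**1. Reproduce the plan's figure.** Weighted mean rate p̄ = (0.15 + 2×0.23)/3 = 0.2033. UC arm: n = [1.960√(1.5 p̄(1−p̄)) + 0.842√(0.15×0.85 + 0.23×0.77/2)]² / 0.08² = 287.9, so 288, and the total is 3×288 = 864. This matches. Power at 900 is 81.7%.

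**2. Unadjusted odds ratio.** OR = (0.23×0.85)/(0.15×0.77) = 1.693 and log OR = 0.526. SE = √[1/(300×0.15×0.85) + 1/(600×0.23×0.77)] = 0.189. So z = 2.79, Wald power is 79.7%, and the 95% CI is exp(0.526 ± 1.96×0.1886) = 1.17 to 2.45.

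**3. Adjusted odds ratio.** Model: logit P = α + βT + sU, with U standard normal and independent of treatment. α and β are solved so that the arm averages stay at 15% and 23%. SE(β) comes from the inverse of the information matrix Σ n_arm·E[p(1−p)ZZ′], with Z = (1, T, sU).

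| s | c-statistic | OR | SE(log OR) | z | Wald power |
|---|---|---|---|---|---|
| 0 | 0.50 | 1.69 | 0.189 | 2.79 | 79.7% |
| 0.5 | 0.63 | 1.73 | 0.192 | 2.85 | 81.2% |
| 0.75 | 0.69 | 1.77 | 0.196 | 2.91 | 82.9% |
| 1.0 | 0.75 | 1.83 | 0.202 | 2.99 | 84.9% |

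The odds ratio and its SE both rise with no confounding present. z rises too, so the test gains power.

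**4. Simulation, 3,000 trials per setting.** The unadjusted OR averages 1.71 (SE 0.190). The adjusted OR averages 1.74 (SE 0.193) at s = 0.5 and 1.85 (SE 0.203) at s = 1.0. Power goes from 81.4% to 83.0% and from 82.4% to 86.9%. The adjusted OR exceeded the crude one in 72% and 86% of single trials.

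**5. Standardized risk difference from the same adjusted model.** The mean stays at 8.0 points. Its SD falls from 0.0272 to 0.0267 (s = 0.5) and from 0.0274 to 0.0256 (s = 1.0). The variance ratios are (0.0272/0.0267)² ≈ 1.04 and (0.0274/0.0256)² ≈ 1.15, equivalent to 4% and 15% more patients. Separate simulations put the range at 2–13% and at 4–12% (c-statistic about 0.66 to 0.75). As a check, write q₀ and q₁ for the abstinence probabilities given U in the two arms. Then E[q₀(1−q₀)]/300 + E[q₁(1−q₁)]/600 + Var(q₁−q₀)/900, set against the crude variance, gives gains of 4% and 14%.

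**6. Why the covariates must be baseline ones.** Assume outpatient service use of 5% in UC and 35% in AR + IVR (the article gives no expected uptake by arm). If use carries 2, 4, 6 or all 8 of the 8 points, adjusting for it lowers the treatment OR from 1.69 to 1.46, 1.28, 1.13 or 1.00.

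**The case against.** The strongest reply is that the motive for adjusting is largely right and the consequence small. Adjustment does gain power, it does deal with chance imbalance, and the same model gives a more precise risk difference. The shift of about 0.04 to 0.14 in the odds ratio is minor beside a confidence interval of 1.17 to 2.45. The article never says that a difference between Models 1 and 2 will be read as confounding. All of this stands, and it limits the point to the stated rationale and the reporting of a secondary analysis.

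Four stronger readings that a reader might infer are not supported:

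- *The adjusted result is only a change of scale.* No: log OR grows faster than its SE (z from 2.79 to 2.85–2.99).
- *The adjusted odds ratio is bound to be larger.* No: with baseline covariates that is usual, not certain. With the service-use variables in the model it may well be smaller.
- *The cost per quit has no usable denominator.* No: the crude difference in proportions supplies it without bias. Only the covariate-adjusted version is missing. Nor is the design purely on the risk-difference scale, since it is an odds ratio of 1.65 that "results in a 23% expected abstinence rate for the AR + IVR group".
- *The primary test or sample size is at fault.* No: Model 1 is unadjusted and 864 reproduces.

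It may also be said that the choice of effect measure belongs in an analysis plan that is not shown. That is fair for the reporting detail. It does not excuse a rationale that the article states and that is wrong for the estimate concerned.

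**Conclusion.** The point holds in a limited form. For the log odds ratio of Model 2, the stated gain in precision is wrong: the SE rises by about 2% to 7%, from 0.189 to 0.192–0.202. Reducing confounding is the wrong description in a trial whose own text expects balanced arms. Models 1 and 2 estimate different odds ratios, one marginal and one conditional, and a gap between them does not show that the crude result was confounded.

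The direction of the SE change held throughout the range examined. The sizes depend on the assumed covariate strength, which the article does not give. Because Model 2 includes a site-by-treatment term, no single coefficient in it is the overall effect unless coding or averaging is stated. That is a further reason to report an averaged effect.

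**What to change.** 1. Reword the rationale in Specific Aim 1: adjustment gains power and handles chance imbalance. It does not remove systematic confounding or shrink the SE of the log odds ratio. Add that Models 1 and 2 estimate different odds ratios and are not to be compared as evidence of confounding.
2. Limit the adjusted model for the treatment effect to baseline covariates. Leave out the program and medications used, which arise after randomization and lie on the path from treatment to abstinence.
3. From that model, without interactions, average the predicted abstinence over all participants under each arm. Report the difference with a 95% CI (delta method or bootstrap) beside the odds ratio.
4. Use this standardized difference for the incremental quits in the cost per quit.
5. Keep the site-by-treatment test as a separate analysis.

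The cost is a few lines of code, a short change of text and one more estimate to report. The sample size and the primary test do not change.

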### Setting

Participants will be recruited from KPNW Sunnyside Medical Center and OHSU hospital in Portland, Oregon. KPNW is a federally qualified, not-for-profit HMO serving more than 470,000 members in northwest Oregon and southwest Washington through one hospital and 26 medical offices. It is an integrated, group-model health-delivery system that provides and coordinates the entire scope of care for its members, including access to a range of tobacco-cessation services through its Health Education Department. Existing inpatient tobacco-cessation services encourage patients with pneumonia, chronic heart failure, and ischemic heart disease to quit and enroll in cessation services upon discharge. OHSU is an academic health center serving a multistate area with specialty tertiary health-care services. OHSU has an existing inpatient tobacco-cessation consult service provided to patients referred by hospital staff: the service includes encouragement to use outpatient cessation services and a single follow-up call shortly after discharge.

KPNW and OHSU have comprehensive EMR systems and have established tobacco-free campuses. In 2010, the Oregon legislature mandated that all Oregon commercial health insurance plans provide a $500 benefit for tobacco-cessation counseling and FDA-approved medications. Oregon’s Medicaid program already provides comprehensive coverage.

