where combined effects, for example, **S**cX_k_, indicate an interaction. Not shown here are the multiple slope coefficients on the vectors of **M** and **G** covariates. We will test the assumption of linear relationships between quantitative covariates and the logit of smoking status by adding quadratic terms to Model 2. The test of homogeneity of covariate regression slopes across conditions and sites is the test that the associated parameter (for example, γ_11_) is 0. When the covariates were measured at baseline, this is a test of whether the variable moderates treatment response. This could provide useful information on subgroups of smokers for whom the intervention is more or less effective.

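### The adjusted Model 2 for Aim 1 is mis-specified for two hospitals: its random site terms are not identifiable, its treatment coefficient depends on an unstated coding, and it has no term for patient-level moderation

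*Protocol article*

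**What the plan says.** All references are to the protocol article.

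- **Sites.** Setting: "Participants will be recruited from KPNW Sunnyside Medical Center and OHSU hospital in Portland, Oregon". Randomization: "Each site randomly assigns 450 patients on a 2:1 ratio", that is, 300 to AR + IVR and 150 to UC at each hospital.
- **Primary test.** Specific Aim 1 uses Model 1, a logistic regression with an intercept and a treatment term, tested by the score chi-square. The article notes that "Model 1 specifies only one source of systematic variation among the trial conditions".
- **Adjusted analysis.** Site, site-by-treatment and measured covariates are then added, to lessen confounding and sharpen the treatment estimate: "With covariates at two levels and patients nested within sites, we shift to a two-level generalized linear model with logit link". Model 2 contains the site indicators Sc (one fewer than the number of sites), site-level covariates Gc, treatment Xk and patient covariates Mi. It has the products ScXk, GcXk, ScMi and GcMi, and the site residuals u0c, u1c and u2c.
- **Moderation.** Of the test that slopes are equal across conditions and sites, the article says: "When the covariates were measured at baseline, this is a test of whether the variable moderates treatment response".
- **Group-level covariates.** Covariates and effect modifiers lists site itself, insurance type, inpatient care unit, cessation program used and medications used.

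**The concern.** With two hospitals, one indicator and its products with treatment and covariates already describe everything that can differ between sites. Random site terms on top have nothing left to estimate, and a covariate that is constant within hospital repeats the indicator.

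Three consequences follow:

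- The two-level model that is announced is not the one that software would fit.
- The coefficient a reader would naturally take as the adjusted treatment effect may belong to one hospital only. This matters because the Discussion expects the two health systems to differ.
- The moderator results, which Randomization relies on when it defers variation in patient factors to the analysis, cannot come from the printed equation.

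The form also spreads. Specific Aim 2 reuses the Aim 1 model for dose-response, and Specific Aim 4 recasts Models 1 and 2 as Poisson models.

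**Working it through.** **Inputs from the article.** Two sites, 300:150 at each; abstinence 15% (UC) and 23% (AR + IVR); two-sided α 0.05; 80% power; no continuity correction. Hospital-specific rates are not given, so those used below are assumptions.

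**1. The plan's own figure.** With pooled variance and 2:1 allocation, p̄ = (0.15 + 2 × 0.23)/3 = 0.2033.

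n(UC) = [1.96√(1.5 × 0.2033 × 0.7967) + 0.8416√(0.15 × 0.85 + 0.23 × 0.77/2)]² / 0.08² = (0.966 + 0.391)²/0.0064 ≈ 288.

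The total is 3 × 288 = 864, as stated in Power. Power at 900 is 0.817.

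**2. Identifiability.** Take one patient covariate M.

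- The fixed terms 1, S, X, SX, M, SM are 6 columns of rank 6.
- The columns for u0c, u1c and u2c are (1−S), S, (1−S)X, SX, (1−S)M and SM. Each is a linear combination of the fixed terms. Together there are 12 columns, still of rank 6.
- Adding G, GX and GM with G constant within hospital gives 9 columns, still of rank 6. Site-level G is aliased with S.

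The likelihood agrees. I kept the fixed site and site-by-treatment terms, used expected counts at assumed UC rates of 12% and 18% with a common odds ratio, and gave u0c and u1c the same SD:

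| SD of site terms | Profile log-likelihood |
|---|---|
| 0 | −445.78 |
| 0.1 | −446.63 |
| 0.2 | −447.79 |
| 0.5 | −450.31 |

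The maximum is at zero variance.

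**3. What the treatment coefficient means.** Under 0/1 coding, γ10 is the log odds ratio at the hospital coded 0. With 15% v 23% at both hospitals, the log OR is ln[(0.23/0.77)/(0.15/0.85)] = ln 1.693 = 0.526.

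- One hospital (150 v 300): SE = √[1/(150 × 0.15 × 0.85) + 1/(300 × 0.23 × 0.77)] = √(1/19.125 + 1/53.13) = 0.267; z = 1.97; Wald power about 0.50.
- Both hospitals (300 v 600): SE = 0.267/√2 = 0.189; z = 2.79; Wald power about 0.80.
- Effect-coded site with the interaction kept: SE 0.189, power about 0.80.

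If effects differ, the estimate moves too. Assume UC 15% at both sites and AR + IVR 27% and 19%. The site odds ratios are (0.27/0.73)/(0.15/0.85) = 2.10 and (0.19/0.81)/(0.15/0.85) = 1.33. Their average on the log scale is (0.740 + 0.285)/2 = 0.512, an odds ratio of 1.67. With the first hospital as reference, γ10 reports 2.10.

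**4. Moderation.** The products printed in Model 2 are S×X, G×X, S×M and G×M. There is no X×M. A test on S×M asks whether a covariate's relation to quitting differs between hospitals, not whether it changes the treatment effect. The γ11 example in the article tests moderation by site only.

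**5. Site left out of Model 1.** 100,000 simulated trials per row, 300:150 at each site. Power uses a common odds ratio of 1.693. The stratified comparator is the Cochran–Mantel–Haenszel test.

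| Assumed UC rates at the two sites | Type I error, Model 1 | Power, Model 1 | Power, stratified by site |
|---|---|---|---|
| 15% / 15% | 0.050 | 0.817 | 0.817 |
| 12% / 18% | 0.050 | 0.813 | 0.815 |
| 10% / 20% | 0.048 | 0.802 | 0.809 |
| 5% / 25% | 0.043 | 0.739 | 0.774 |

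**The case against.** The strongest reply is that none of this touches the primary test. That stands. Model 1 can be fitted, allocation is 2:1 at both hospitals so site does not confound it, and its error rate is never above nominal in the table apart from simulation noise. The small gap between the log OR without site (0.514) and with site (0.526) at assumed UC rates of 10% and 20% is the usual difference between a marginal and a conditional odds ratio, not a bias.

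Four stronger readings are tempting, and the article does not support them:

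- *Model 2 cannot be fitted at all.* Software may instead set the site variances to zero and return an ordinary fixed-effects model. The terms are redundant; failure is only one possible result.
- *The adjusted effect is one hospital's effect.* This needs 0/1 coding and γ10 read as the overall effect. The first is the natural sense of an indicator, but the article states neither, and coding is often left to an analysis plan.
- *The trial's power falls to about 50%.* That figure applies only to γ10 under that coding, not to the primary test.
- *All listed group-level covariates are aliased with site.* Only site itself necessarily is. Table 1 shows insurance type varying within each hospital, so such items are misclassified, and their products with treatment could be estimated.

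On moderators, the article does promise treatment effects by sex and race/ethnicity and admits limited power. That makes the gap exploratory, but the claim made for the printed model is still wrong.

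**Conclusion.** The point holds for the adjusted and moderator analyses, as a should-fix.

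- The site random terms are not identifiable beside the fixed site terms. This follows from the printed equation and the number of sites, with no further assumption.
- Site appears both as Sc and in the list for Gc, so it is aliased with itself. The other listed items vary between patients and are not site-level.
- Under 0/1 coding, the treatment coefficient has an SE about 1.41 times as large (0.267 v 0.189) at 15% v 23% in both hospitals, the opposite of the stated aim. The article names no coding or contrast that would prevent this.
- Moderation by patient-level covariates in M cannot be tested with Model 2 as printed.

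A reader might infer from the by-site randomization that leaving site out invalidates the primary result. It does not: the omission is slightly conservative. It costs under 1 point of power for assumed UC rates up to 10% v 20%, and about 3.5 points at an extreme 5% v 25%. The sample size is unaffected.

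**What to change.** Rewrite the Model 2 paragraphs:

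1. Drop u0c, u1c and u2c and the site-level vector G.
2. Fit the adjusted model as logistic regression on treatment, site as a fixed effect, and pre-specified patient-level baseline covariates. Insurance type and care unit move to the patient level. Program and medication use also vary between patients, but use after randomization is not a baseline covariate.
3. Test site-by-treatment in a separate model with 1 degree of freedom and report the effect at each hospital. If the interaction stays in the main adjusted model, state an effect-coded or averaged contrast for the overall effect.
4. Test moderators with explicit treatment-by-covariate terms.
5. As a free improvement, add site as a fixed effect to the primary model. The odds ratio then becomes conditional on site (1.693 against 1.672 at assumed UC rates of 10% and 20%).
6. Carry the corrected form into Aims 2 and 4.

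The cost is a redrafted model section and less programming than now planned. It needs no new data and no change in sample size.
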